### 2.3. Sample Size Calculation

The sample size was determined using Encyclopaedia Medical Statistics 3.2 software (PEMS 3.2, Guangzhou Jing far Pharmaceutical Research Co., Ltd., Guangzhou, China) with 90% power and a significance level of 0.05 (two-sided). According to Lizogub et al. [30], the sample size should consist of 50 participants in each group. Considering the potential 20% loss, 60 participants are needed for each group. As there is a low-dose group, a middle-dose group, a high-dose group, and a control group with five centers involved, a total of 240 participants will be recruited in this study, with 48 patients recruited at each center.

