#### 2.6.5. Primary Outcomes

*Duration of All Symptoms*. Duration of all symptoms is defined as the number of days from enrollment to the day that all symptoms disappear (the time from the symptom severity score above zero until 2 days of the severity score marked as zero). If symptom severity is marked above zero on the day after a single day of zero, the cold is defined as continuing. If the day marked above zero is the 11th day, this is defined as the end of the cold, but if symptoms last more than 11 days, follow-up will continue via phone call or e-mail until all symptoms are absent. The first day of medication administration is defined as the 1st day (day 1) in the study. The start of the day is defined as 6:00 a.m., and symptoms absent before 6:00 a.m. are regarded as occurring the day before.

Because all the participants in the trial have Qi-deficiency syndrome and normally present certain Qi-deficiency symptoms (fatigue, shortness of breath, and spontaneous perspiration), we define the disappearance of Qi-deficiency symptoms (symptom score = 0) (Table 2) as all the symptoms returning to the basic level present before the onset of common cold.

*The Total Score Reduction of Jackson's Scale*. Jackson's scale [27], which is specific for diagnosis and symptom severity assessment of common cold, contains 8 symptoms (sneezing, headache, malaise, chilliness, nasal discharge, nasal obstruction, sore throat, and cough) and rates as 0 = absent, 1 = mild, 2 = moderate, and 3 = severe. The symptom score will be summed on the 1st day and the 4th, 6th, and 11th days after intervention, and the score reduction will be calculated between the 1st day and the days after the intervention.

The symptom severity and score are assessed by researchers who are blind to the trial, and one participant is assessed by the same researcher consistently throughout trial. Participants will not be allowed to assess their overall illness or level of severity to avoid assessment bias.

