### 2.8. Statistical Analysis

The full analysis set (FAS) is the primary analysis set for efficacy with an intention-to-treat (ITT) principle. In the FAS, all patients will be treated with at least one dose of the study drug and at least one clinical observation will be recorded in the study. All subjects without any major protocol deviations will be involved in the per-protocol set (PPS). The safety analysis will be conducted for randomized subjects who have completed at least one study visit and have safety data. Descriptive statistics will be performed on continuous variables, frequencies, and categorical variables. All symptom durations, total score reductions on Jackson's scale and TCM symptoms, the duration of each TCM symptom, the decreasing rate of TCM main symptoms, and the reduction score of TCM symptoms will be estimated with the Kaplan-Meier technique and compared using the stratified log-rank test. Comparisons among different dose groups and age layers will be conducted with an analysis of variance (ANOVA) and a least significant difference *t*-test. In this multicenter trial, the Cochran-Mantel-Haenszel test stratified by clinical centers and the logistic regression model adjusted for covariates will be used. Statistical analyses will be conducted by an independent statistician from the Health Statistics Department of the Fourth Military Medical University using the SAS statistical software 9.1.3 (SAS, Cary, North Carolina State University, North Carolina, USA).

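### Section 2.8 does not limit ANOVA and LSD t-tests to the score outcomes, so pairwise dose comparisons of the primary symptom duration may rest on tests that cannot handle unresolved durations

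*Protocol article*

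**What the plan says.** The first of the three primary outcomes is a time to event (section 2.6.5): "Duration of all symptoms is defined as the number of days from enrollment to the day that all symptoms disappear".

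Section 2.8 then has two consecutive sentences on methods:

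- The first opens its list with "All symptom durations, total score reductions on Jackson's scale and TCM symptoms, the duration of each TCM symptom", continues with further score-type outcomes, and says that they "will be estimated with the Kaplan-Meier technique and compared using the stratified log-rank test".
- The second says "Comparisons among different dose groups and age layers will be conducted with an analysis of variance (ANOVA", and adds an LSD t-test. It names no outcome and excludes none.

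Three other places bear on how a duration can end up unresolved or very long:

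- Section 2.3 sets the sample size with an allowance for attrition: "Considering the potential 20% loss, 60 participants are needed for each group".
- Section 2.2.4 withdraws patients who have not improved, or have worsened, after 72 hours on study drug, and keeps them in the full analysis set. Section 2.8 makes that set primary for efficacy.
- Section 2.6.5 has two rules about Day 11: "If the day marked above zero is the 11th day, this is defined as the end of the cold", and "if symptoms last more than 11 days, follow-up will continue via phone call or e-mail until all symptoms are absent".

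**The concern.** Finding the best dose is a stated aim of the trial, and LSD is the only method that section 2.8 names for comparing pairs of groups. If the second sentence covers durations, the dose answer for a primary time-to-event outcome comes from t-tests.

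A t-test needs a completed duration for every patient. A patient who leaves before recovery must either be left out or be given the leaving day as if it were the recovery day. The second option turns a treatment failure into a short cold. The log-rank test can instead count the patient as at risk up to the leaving day.

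The two methods can therefore give different answers for the same arms. The plan does not say which one governs, so the choice could be made after the results are seen.

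**Working it through.** **1. Does the text divide the outcomes between the two methods?** If the first sentence listed only durations, the second could be taken to cover the scores by default. It does not: durations and score reductions stand in one list, all assigned to Kaplan-Meier and log-rank. Reading ANOVA as meant for scores alone is plausible as intent, but nothing printed supports it. The list also shows a second fault: a score reduction is not a time, so Kaplan-Meier and log-rank do not suit it.

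**2. How many durations could be unresolved?** The allowance in section 2.3 amounts to 0.20 × 60 = 12 patients per group, or 0.20 × 240 = 48 in all. It is a planning allowance, not a forecast of loss before recovery. The 72-hour rule adds a route by which unresolved patients stay in the primary analysis set.

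**3. How long is the tail?** The introduction says that colds typically last 7–10 days but can persist for several weeks. If one cold in an arm of 60 lasts 28 days (assumed) instead of 7, the arm mean moves by (28 − 7)/60 = 0.35 day. If the Day 11 end rule is applied as a cap, the most that one such cold can add is (11 − 7)/60 = 0.07 day. The influence of long colds thus depends on which of the two Day 11 rules is used.

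**4. Planning inputs.** The 50 per group cannot be reproduced, because the article gives no effect size, SD or hazard ratio. Back-solving for two means at two-sided 0.05 and 90% power gives a standardised difference of (1.960 + 1.282) × √(2/50) = 0.65. That does not supply a distribution of durations, so every scenario below is an assumption.

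**5. Simulation A.** Inputs: four arms of 60; lognormal durations in whole days; medians all 8 (null) or 8/7.3/6.7/6 (effect); 1,500 runs; unstratified four-group log-rank against one-way ANOVA on observed days, with the leaving day used as the duration. Loss means a 20% chance of a leaving day, uniform on days 2 to 10, counted only if it precedes recovery. The unresolved share is therefore below 20%.

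| Scenario | Log-SD | Log-rank rejects | ANOVA rejects | Tests disagree |
|---|---|---|---|---|
| Null, no loss | 0.4 | 6.6% | 6.0% | 1.3 + 0.7 = 2.0% |
| Null, no loss | 0.6 | 6.4% | 5.7% | 1.3 + 0.5 = 1.8% |
| Effect, no loss | 0.4 | 90.0% | 92.0% | 0.5 + 2.5 = 3.0% |
| Effect, no loss | 0.6 | 53.9% | 52.3% | 3.9 + 2.3 = 6.2% |
| Null, loss | 0.4 | 5.7% | 4.1% | 3.4 + 1.8 = 5.2% |
| Null, loss | 0.6 | 5.7% | 4.1% | 3.1 + 1.5 = 4.6% |
| Effect, loss | 0.4 | 87.5% | 81.1% | 9.1 + 2.7 = 11.8% |
| Effect, loss | 0.6 | 53.0% | 43.1% | 13.6 + 3.7 = 17.3% |

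With an effect and loss, the power gaps are 87.5 − 81.1 = 6.4 and 53.0 − 43.1 = 9.9 points.

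**6. Simulation B.** Inputs: one dose against control; 60 per arm; Weibull durations with median 7 days; hazard ratio 1.9; 19% lost; 5% of colds lasting 14–28 days; 10 strata; 800 runs.

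| Weibull shape | Stratified log-rank | t-test, completers | t-test, leaving day as duration | Gap to log-rank (points) |
|---|---|---|---|---|
| 2.5 | 66% | 48% | 46% | 18 and 20 |
| 2.0 | 65% | 53% | 52% | 12 and 13 |
| 1.5 | 69% | 68% | 69% | 1 and 0 |

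The Monte Carlo standard error near 50% power is √(0.25/1500) = 1.3 points in A and √(0.25/800) = 1.8 points in B.

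**7. Unequal withdrawal.** Two further runs with the design of A (log-SD 0.4) had withdrawal on day 4 at different rates by arm.

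- Equal true durations, withdrawal 25% in control and 10% in each dose group: ANOVA rejected in 18.3% of trials, log-rank in 5.9%.
- Real effect, withdrawal 30/20/15/10%: power was 25.6% for ANOVA and 86.4% for log-rank.

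Withdrawal in these runs was unrelated to prognosis. Withdrawal for lack of improvement would be related to it, and log-rank would then be biased too. These runs show a direction only and are not used for the size.

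**The case against.** The strongest reply is that no sentence applies ANOVA to duration. Durations are expressly assigned to log-rank, and a specific assignment ordinarily overrides a general sentence. This stands in part. A reader might infer that the first primary outcome is definitely tested twice, and the document does not say so. It does permit that reading, and the mixed list in the first sentence removes the textual basis for the narrower one.

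Second, the article names three dose groups and, separately, a control group. The ANOVA sentence may therefore cover only active doses, with log-rank used against control. That is possible, so it is not shown that both tests address the same contrast. The point survives, because dose against dose is the dose-selection question and would then be answered by t-tests alone.

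Third, a reader might infer that the two tests would use different patients, or that type I error is inflated because success on either test would count. Neither is supported. The full analysis set is primary, nothing says that ANOVA uses completers or leaving days, and no either-test rule is stated.

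Fourth, censoring may be light: patients are contacted daily and colds past Day 11 are followed to resolution. With complete follow-up the tests nearly agree. This limits the size of the problem.

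Finally, an article may leave detail to an analysis plan. Here, however, the article does assign the methods, and does so without a workable division.

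**Conclusion.** The point holds as a fault of assignment in section 2.8. As printed, pairwise dose comparisons of a primary time-to-event outcome may be made by t-tests that cannot use unresolved durations, and nothing says which test decides. The same passage also puts score reductions under a method for times.

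The size cannot be derived from the document. The tests disagree in about 2–6% of simulated trials with complete follow-up. With about 20% early loss unrelated to arm, the power difference runs from roughly 0 to 20 points. That range rests on assumed medians, spread, Weibull shape, hazard ratio, loss and share of long colds. No single power loss should be quoted as the trial's own.

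Log-rank is the better choice for durations but does not cure everything, since withdrawal for lack of improvement is informative and biases it as well. The change is worth making before analysis because it removes a choice between tests at almost no cost.

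**What to change.** Amend section 2.8 in three places:

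- **Durations.** Compare all symptom durations, overall and for each pairwise dose and dose-versus-control contrast, by log-rank or Cox stratified by centre and age layer, and name this as the deciding analysis.
- **Scores.** Restrict ANOVA/LSD, or a linear model in its place, to the symptom-score reductions.
- **Log-rank list.** Remove the score reductions from the outcomes assigned to Kaplan-Meier and log-rank, so that each outcome has one method.

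The cost is a few sentences, with no extra data or patients.

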## 3. Discussion

There is an urgent necessity to develop an effective treatment for CCQDS due to its frequent occurrence and heavy burden. This study intend to examine the clinical efficacy and safety and find optimal dose of SGLNG for treating CCQDS, in a randomized, double-blind, and placebo-controlled trail.

We conduct this study not only to propose a new remedy for common cold, but also to practice the methodology of syndrome differentiation for clinical research in TCM. This is the first study that addresses the efficacy and safety of a TCM formula for this specific but frequently seen TCM syndrome, Qi-deficiency in common cold in a double-blind and placebo-controlled trail. We assume that this design, which is in line with TCM theory and also typical of individualized and phenotype-based medicine, will contribute to more convincing results and robust evidence for the efficacy of study medications and cause new insight into common cold treating. Apart from the syndrome differentiation-based selection of the study population, there is another strength in this study. We perform both Western and TCM scales to measure the effects of the study medication. They are overlapping in terms of certain symptoms, while TCM symptoms cover some other abnormal symptoms than Jackson's scale, but the relationship between them has not been explored before. In this study, the scores of Jackson's scale and TCM symptom scale are compared at each time point, so as to detect their merit and weak point, respectively, which may provide more powerful evidence for further measurements of common cold. To our knowledge, this is the first trial to evaluate the difference between Jackson's scale and TCM symptom scale.

There are some limitations in this study. Due to limited budget, we do not perform culture assessing for inclusion of patients with common cold, which may cause mistakenly recruiting patients with potential influenza. To minimize this mistake, all the clinical researchers involved in the study are educated on the difference between common cold and influenza. Patients who experience severe symptoms will be excluded at enrollment, while those with symptoms which were slight at first but worsened rapidly during the study will be advised for culture assessing in clinical or even dropout from the trail. Apart from that, we employ Jackson's scale for the outcome measurement, while other latest questionnaires such as the Wisconsin Upper Respiratory Symptom Survey [31] would be useful. However, we did not include this questionnaire due to the unavailability of a Chinese version. Additionally, the study trail does not cover the mechanisms underlying CCQDS and potential pathways through which TCM formula can treat the disease in this specific population, which still require further detection.

In summary, by rigorous methodology for a clinical trial and syndrome differentiation-based approach, the results of this study will provide robust clinical evidence regarding the efficacy, safety, and optimal dose of SGLNG for treating CCQDS.

## 4. Conclusion

This trial asks if SGLNG reduces CCQDS symptoms and which is the optimal dose.

## Figures and Tables

**Figure 1 fig1:**
[figure not shown]
Flowchart. 240 patients will be recruited in the study and randomly allocated to one of four groups (high-dose group = 60; middle-dose group = 60; low-dose group = 60; control group = 60). After 5 days of treatment, we analyze the data collected and make conclusion.

**Table 1 tab1:** Formulation and dose of SGLNG.

Chinese Pinyin name	English name	Latin name	Source	Weight (%)^*∗*^
Hua Xiang Shu Guo Xu	Infructescence of Platycarya strobilacea Sieb.	Platycarya strobilacea sieb.et Zucc	The dried infructescence of *Platycarya strobilacea* Sieb.	14.96
Hu Zhang	Polygonum cuspidatum	Polygonum cuspidatum Sieb.et Zucc	The dried rhizome and root of Polygonum cuspidatum	11.97
Gui Zhen Cao	Bidens bipinnata	Bidens pilosa L.	The dried stems and leaves of *Bidens bipinnata*	14.96
Ye Ju Hua	Mother Chrysanthemum	Dendranthema indicum	The dried flowers of Mother Chrysanthemum	11.97
Ma Huang	Ephedra	E. sinica Stapf	The dried herbaceous stem of Ephedra	5.98
Luo Hang Guo	Siraitia	Siraitia grosvenorii	The dried fruit of *Siraitia*	14.96
Xi Yang Shen	American ginseng	Panax quinquefolius	The dried root of American ginseng	2.99
Xiang Gu	Mushrooms	Lentinus edodes	The dried mushrooms without roots	11.97
Huang Qi	Astragalus membranaceus	Astragalus membranaceus Bunge	The dried stems and leaves of Astragalus membranaceus	9.97

^*∗*^The weight of every single herb in each bag of SGLNG (5 g).

**Table 2 tab2:** TCM symptoms of common cold and symptom score.

		Symptom^*∗*^	None = 0	Mild = 2	Moderate = 4	Severe = 6
Main symptom	(1)	Aversion to cold	None	Slight aversion to cold, do not need to add cloth	Aversion to cold, need to add cloth	Aversion to cold, need to add thick cloth, or bedding
		Stuffy and running nose	None	Mild nasal congestion, runny nose occasionally, not affecting respiration	Nasal congestion, runny nose, affecting breathing	Obvious nasal congestion, running nose, mouth breathing
	(2)	Fatigue	None	Lack of energy, not resistant to labor, (slight heavier than usual)	Mental weariness, slightly affecting daily activities (heavier than usual)	Limb weakness, cannot support daily activities (much heavier than usual)
		Short of breath	None	Shortness of breath after labor (slight heavier than usual)	Shortness of breath after slight labor (heavier than usual)	Obvious shortness of breath when resting (much heavier than usual)

		Symptom	None = 0	Mild = 1	Moderate = 2	Severe = 3

Secondary symptom		Fever	None	37.3–37.5°C	37.6–37.9°C	≧38.0°C
		Sore throat	None	Dry throat with slight pain	Significant with obvious pain when swallowing	Sore and swollen throat with severe pain
		Headache	None	Slight and occasionally	Severe and lasting	Severe and affect working
		Cough	None	Occasionally in daytime, not affecting daily life	Occasionally day and night, slightly affecting sleep	Frequent cough day and night, affecting rest and sleep
		Expectoration	None	Stick sputum, not easy to cough out	Stick or yellow sputum	Stick or yellow sputum with large volume
		Spontaneous perspiration	None	Yes (severe than usual)	—	—
		Tongue and pulse condition^#^	Tongue color	Pale □ Red □		Others
			Tongue coat	Thin white □ Thin yellow □		Others

^*∗*^Scores represent the severity of symptoms. ^#^The score of tongue and pulse will not be recorded.

**Table 3 tab3:** Study schedule for patients. On the 1st day, researchers collect the data of medical and treatment history, efficacy observation, safety assessment, and exclusive observation of patients, as well as randomization, allocation, and drug distribution. On the 4th day (fulfilled for 4 days to the first time of medicine consume), patients take the second visit for physical examination, and researchers record symptoms scores, combined medication, and adverse event (if any). The 6th ± 1 day (fulfilled for 6 days to the first time of medicine consume), patients take the third visit for physical examination and the second safety assessment, and researchers record symptoms scores, combined medication, adverse event (if any), and recycled medicines and pack box, and drug quantity statistics. On the 11th ± 2 day (fulfilled for 11 days to the first time of medicine consume), patients take the fourth visit for physical examination, and researchers record symptoms scores, combined medication, and adverse event (if any).

Stage	Visit period			
Treatment	Visit 1	Visit 2	Visit 3	Visit 4
Day	1 day	4th day	6th ± 1 day	11th ± 2 days

*Basic medical history recording*				
Informed consent signing	×			
General information recording	×			
Medical and treatment history recording	×			
Complication and symptoms recording	×			
Physical examining	×	×	×	×
Combined medication recording		×	×	×
*Efficacy observation *				
Symptoms scores recording	×	×	×	×
*Safety assessment *				
Routine blood test	×		×	
Routine urine + urinary sediment microscopy	×		×	
Liver function test	×		×	
Renal function test	×		×	
Fasting blood glucose + 2 h postprandial blood glucose	×		×	
Electrocardiogram	×		×	
*Excluding observation *				
Chest X-ray	×			
Urine pregnancy test (female)	×			
Fasting blood glucose + 2 h postprandial blood glucose	×			
*Adverse events observation *				
Adverse event recording		×	×	×
*Other works *				
Randomization and allocation	×			
Drug distribution	×			
Medicines and packing box recycling			×	
Drug quantity statistics			×	

## Abbreviations

ALB: Albumin
ALP: Alkaline phosphatase
ALT: Alanine transferase
ANOVA: Analysis of variance
AST: Aspartate transferase
CAM: Complementary and alternative medicine
CCQDS: Common cold with Qi-deficiency syndrome
Cr: Creatinine
CRF: Case report form
ECG: Electrocardiogram
FAS: Full analysis set
GMP: Good manufacturing practices
ITT: Intention-to-treat
PPS: Per-protocol set
PSSR: Percentage of cumulative TCM symptom score reduction
*γ*-GT: *γ*-Glutamyltranspetidase
SFDA: State Food and Drug Administration
SGLNG: Shen Guo Lao Nian Granule
TBIL: Total bilirubin
TCM: Traditional Chinese medicine
URTI: Upper respiratory tract infection
USA: United States of America.
